**Sample size and study group selection**

Applying these criteria, 50 HIV-infected adult outpatients who had never been vaccinated with any pneumococcal vaccine will be prospectively enrolled at two Infectious Diseases Clinical Centers in Central Italy (University Division of Infectious Diseases in Siena and Institute of Clinical Infectious Diseases, Catholic University of the Sacred Heart in Rome). All subjects will be required to sign a written informed consent before enrolling in the study.

At baseline (day 0, time of first vaccine dose administration), demographic, clinical and laboratory characteristics will be collected by patients interview.

At baseline, the enrolled patients will received two doses of the 13-valent vaccine (PCV13 Prevenar13®, Wyeth Vaccines) eight weeks apart.

Follow-up visits will be scheduled at 8 (time of second PCV13 dose), 24 and 48 weeks. At baseline and at each visit clinical and anamnestic data from patients will be recorded; peripheral venous blood samples will be collected to assess humoral immune response against PCV13 serotype; nasopharyngeal swabs will be collected, in order to investigate the *S. pneumonia* presence. CD4+ T cell count and plasma HIV-RNA will be also monitored.

After each vaccine administration, short- (30 minutes), medium- (≤5 days) and long-term adverse reactions will be monitored.

**STUDY METHODOLOGY**

**Immunological evaluations**

Sera collected from all patients will be stored at -20°C until use and they will be tested at Institute of Clinical Infectious Diseases, Catholic University of the Sacred Heart, Rome. Quantitation of specific IgG levels for 13 PCV13 serotypes (1, 3, 4, 5, 6A, 6B, 7F, 9V, 14, 18C, 19F, 19A and 23F) will be performed on sera, by an ELISA method, according to the World Health Organization (WHO) procedure; IgG concentrations will be expressed as geometric mean concentration (GMC).

The generally used threshold of 0.35µg/mL (accepted by the WHO for assessment of vaccine efficacy against IPD) it will be chosen as cut-offs for defining seroprotection levels.

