**RATIONALE**

*S. pneumoniae* is frequently isolated from nasal swabs of healthy subjects, but it can also cause severe diseases (pneumonia, bacteraemia, meningitis and sepsis).HIV-infected subjects are more sensitive to invasive diseases and recurrent infection than the general population. Nasal carriage is the main pathogenetic feature for invasive disease: bacteraemia is more frequent in carriers, HIV+ patients are constantly colonized by the same pneumococcal strain and their nasopharyngeal isolates have features similar to subsequent invasive strains. A 23-valent polysaccharide vaccine (PPV23) has long been available and recommended in the HIV+ population as prophylaxis for invasive disease. Studies regarding efficacy of PPV23 in HIV+ are controversial and highlight that immune response induced by PPV23 in HIV+ is poor and an hyporesponsiveness to repeated polysaccaridic antigens stimulation can occur. Moreover, PPV23 seems not to affect pneumococcal carriage status and could lead to emergence of non-vaccine serotypes. The conjugation of pneumococcal capsular polysaccharides to carrier proteins results in an improved T-cell dependent immune response, characterized by increased antibody concentrations and induction of T and B memory cells, with a demonstrated higher efficacy in children. A heptavalent vaccine conjugated with diphtheria toxoid (PCV7) is approved in Europe since 2001 and is effective in reducing incidence of invasive disease by vaccine serotypes (4, 6B, 9V, 14, 18C, 19F, 23F), in both children and adults, due to effect of herd immunity. A PCV13 formulation has recently been developed, covering PCV7 serotypes plus 1, 3, 5, 6A, 7F and 19A. PCV13 revealed the same safety profile as PCV7 in pediatric patients, that are the main target of conjugate vaccines licensure. Some trials showed a better antibody response in terms of quantity and quality in HIV + adults by using PCV7 as compared to PPV23. However these data were not unequivocally confirmed in further studies on the use of PCV7 alone or in combination with PPV23. The first trials of PCV13 use in adults showed the same or even better response compared to PPV23, with a safety and tolerability similar to PCV7. PCV13 in HIV+ adults is a promising candidate prophylactic measure for pneumococcal infections.

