**Primary Outcome Measures:**

- Define the serological response after 2 doses of PCV13 vaccine. Measure of serological response after 2 doses of PCV13 vaccine (booster dose after 8 weeks) in HIV+ adults.
- Determine the rate of nasopharyngeal colonization by different pneumococcal serotypes in HIV-positive adults, in relation to baseline antibody titers at T0

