**Exclusion Criteria:**

- > 65 years old
- presence of acute infectious disease
- antibiotic therapy (ongoing or in the previous <= 7 days)
- previous PPV23 or PCV7 vaccination
- Pregnancy
- Current immunomodulatory therapy
- Immunosuppression not HIV related

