**STATISTIC ANALYSIS**

Clinical and anamnestic data collected at enrolment and at each follow-up visit, will be integrated with microbiological and serological results and correlation analyses will be performed.

Further statistical analyses will be carried out considering the results from this study and from the sub-study (protocol code PNEUMO-HIV 2011).

To evaluate the immunological response, the geometric mean concentrations of IgG (GMCs) at baseline, 4,8,24 e 48 week will be calculated. The GMCs will be compared by Student's' t Test (For Paired Samples). The quantitative variable will be tested for normal distribution and compared by

Mann-Whitney or Kruskal-Wallis test.

Differences in proportion will be determined by chi squared test or fischer exact test.

Regression or logistic analyses (univariate and multivariate) will asses the association with colonization, infection, antibiotic resistance, and an efficient immune response (e.g. ≥0.35μg/mL).

Analyses were performed using the SPSS software package (version 17.0 Chicago, IL).

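### The only criterion given for an efficient immune response in the regressions is an absolute IgG level with no baseline condition, so patients already above it at T0 can count as responders

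*Supplement*

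**What the plan says.** The same threshold appears in two roles.

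- **As a state at a visit.** Immunological evaluations (main study and sub-study) adopts 0.35 µg/mL, and "it will be chosen as cut-offs for defining seroprotection levels".
- **As a response.** Statistic Analysis (both protocols) lists the outcomes of the univariate and multivariate regression or logistic models. The last of them is "an efficient immune response (e.g. ≥0.35μg/mL"). The level is offered as an example, and no other criterion is given.

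The first primary outcome of the main study is to "Define the serological response after 2 doses of PCV13 vaccine", with no responder rule attached. The second is the colonization rate "in relation to baseline antibody titers at T0", so the plan regards T0 titres as informative.

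Baseline sera will exist. Under Sample size and study group selection: "At baseline and at each visit clinical and anamnestic data from patients will be recorded; peripheral venous blood samples will be collected". Eligibility sets no limit on baseline titre; in the main study the relevant exclusion is "previous PPV23 or PCV7 vaccination".

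Baseline does enter one analysis: Statistic Analysis compares GMCs by a paired t test.

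**The concern.** A concentration measured after vaccination is not in itself a response to vaccination. Under the only criterion given, a patient at 0.8 µg/mL at T0 and 0.8 at week 24 is a responder. A patient who rises 6-fold, from 0.05 to 0.30, is not.

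The documents make antibody before vaccination plausible. The Rationale calls carriage frequent in healthy people and says that "HIV+ patients are constantly colonized by the same pneumococcal strain". A vaccine-naïve patient can therefore have naturally acquired antibody to some serotypes.

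Two results are at stake. A per-serotype proportion reported as vaccine response would include people who met the cut-off before the first dose. A logistic model of that outcome, without the T0 titre, could report predictors of prior antibody as predictors of vaccine response.

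**Working it through.** The plan states no responder rate, baseline titre, SD or power, so there is no figure to reproduce. The inputs are:

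- cut-off 0.35 µg/mL (Immunological evaluations; Statistic Analysis);
- N = 50 in the main study (Sample size and study group selection);
- baseline GMC and SD: **not in the documents, assumed**.

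**1. Share meeting the cut-off before any dose.** Take log10 IgG as normal with mean log10(GMC) and SD 0.5. The share at or above the cut-off is 1 − Φ(z), with z = [log10(0.35) − log10(GMC)] / 0.5 and log10(0.35) = −0.456.

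| Assumed baseline GMC (µg/mL) | z | Share ≥0.35 at T0 | Of 50 patients |
|---|---|---|---|
| 0.1 | 1.09 | 14% | 7 |
| 0.2 | 0.49 | 31% | 16 |
| 0.35 | 0.00 | 50% | 25 |
| 0.5 | −0.31 | 62% | 31 |
| 1.0 | −0.91 | 82% | 41 |

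With stable titres and a vaccine that did nothing, these would also be the expected responder rates afterwards.

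**2. Chance that at least half of 50 patients are classed as responders with no vaccine effect** (binomial tail, 25 or more). For assumed baseline shares of 20%, 40%, 60%, 80% and 90%, the chance is <0.1%, 9.8%, 94.3%, >99.9% and >99.9%. The problem is slight for serotypes with little prior antibody and dominant for those with much.

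**3. What a baseline condition changes.** This is a simulation in which every input is assumed: between-patient SD 0.45 log10, measurement error 0.10 log10 and, where there is an effect, a geometric mean 2-fold rise with SD 0.3 log10.

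| Baseline GMC (µg/mL) | No effect: cut-off only | No effect: cut-off and ≥2-fold rise | 2-fold effect: cut-off only | 2-fold effect: cut-off and ≥2-fold rise | 2-fold effect: share of cut-off-only responders already ≥0.35 at T0 |
|---|---|---|---|---|---|
| 0.2 | 30% | 0.7% | 54% | 36% | 51% |
| 0.35 | 50% | 1.1% | 71% | 43% | 67% |
| 0.7 | 74% | 1.4% | 86% | 48% | 83% |
| 1.5 | 92% | 1.6% | 95% | 50% | 94% |

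Under the cut-off alone, the rate for a useless vaccine at a GMC of 0.7 (74%) exceeds that for a vaccine with a true 2-fold effect at 0.2 (54%). The ranking of serotypes then follows the baseline.

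**4. Check on the two endpoints proposed below**, which are separate and not the composite simulated in step 3.

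- *Fold-rise alone, no effect.* The difference of two measurements has SD √(0.10² + 0.10²) = 0.141, so P(≥2-fold) = 1 − Φ(0.301/0.141) = 1.7% at any baseline.
- *Reaching 0.35 among those below it at T0, no effect.* From the simulation, at GMC 0.2, 85.5% of the 29.8% above the cut-off afterwards were already above it. New crossers are 0.298 × 0.145 = 4.3% of all patients, or 4.3/70.2 = 6% of those below. At GMC 0.7 it is 0.742 × 0.053 = 3.9%, or 3.9/25.8 = 15%. Measurement error alone moves some patients across the line.
- *Denominators for the second endpoint.* 50 × 0.702 = 35 at GMC 0.2, 50 × 0.258 = 13 at 0.7 and 50 × 0.085 = 4 at 1.5.

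**The case against.** The best defence has four parts.

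- **0.35 is only an example.** True: the text does not fix it as the definition, nor does it say that baseline is to be ignored. But no other criterion is given, so either this one is used or the rule is chosen later, possibly with the data in view. The remedy is the same.
- **Seroprotection is properly an absolute level.** True. The Immunological evaluations section describes a state at a visit, and a patient above 0.35 at T0 is correctly described as above it. The sub-study even speaks of a basal serological response, so the plan uses the word loosely. The fault arises only where the level becomes a response outcome in Statistic Analysis.
- **Baseline is used where the immunological response is evaluated.** True. The paired GMC comparison takes each patient as their own control and would show no expected rise for an inactive vaccine. The fault is confined to responder proportions and the models of response, in a pilot of 50.
- **The size is unknown.** True: it depends on baseline titres that the documents do not give.

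Three stronger readings are tempting but unsupported. A reader might infer that at least half of the responders would be spurious; that follows only if baseline GMCs are assumed at or above the cut-off. A reader might use prior PPV23 vaccination as evidence of high baselines. It does not apply to the vaccine-naïve main study, and in the sub-study the inclusion and exclusion criteria contradict each other on it and must be reconciled. A reader might also conclude that the PCV13 and PPV23 comparison is biased, but no section specifies comparing the vaccines on the percentage above 0.35.

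**Conclusion.** The point holds in a limited form. In both protocols the only criterion for the binary immune response carries no baseline condition, so a patient already at or above 0.35 µg/mL at T0 with no rise can be counted as a responder. Before any dose, the share meeting it could be about 14% to 82% per serotype, for assumed baseline GMCs of 0.1 to 1.0 µg/mL and a log10 SD of 0.5. The documents cannot narrow that range. The GMC analysis and the use of 0.35 to describe seroprotection at a visit both stand. Responder rates and predictor models built on the example criterion could not be read as vaccine effects. This should be mended before analysis, but it does not undermine the study as a whole.

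**What to change.** Amend Statistic Analysis in both protocols.

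1. Define vaccine response per serotype, among vaccinated participants, as two separate endpoints: (a) a prespecified fold-rise in IgG from the patient's own T0, for example at least 2-fold; and (b) reaching at least 0.35 µg/mL among those below 0.35 at T0. The 2-fold figure is a proposal and not taken from the documents. What matters is that a figure is fixed in advance.
2. Keep the percentage at or above 0.35 as a description of seroprotection, reported at each follow-up visit only beside its T0 value, with a paired confidence interval for the change. The unvaccinated HIV-negative subjects of the sub-study are sampled only at baseline, so for them it is the only one of these measures available.
3. Include T0 log10 IgG as a covariate in every regression of post-vaccination response, including any comparison of the main-study and sub-study populations.

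The cost is wording, since T0 and follow-up sera are already planned. The headline response rate will be lower. The denominator for (b) shrinks where baseline antibody is common, and (b) still admits some crossing by measurement error, so counts should be shown. A fixed fold-rise may miss real responses from high baselines; the T0 covariate and the GMC analysis offset this in part.

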**Microbiological evaluations**

All the isolated strains of *S. pneumoniae* and their genomic DNA will be collected at University Division of Infectious Diseases, Siena.

Swabs will plated on Columbia CNA + 5% blood agar then incubated at 37°C for 16-18 hours in CO2 enriched atmosphere. Bacterial isolates will be identified and processed through standard procedures: small, α-hemolythic, “draughtsman” colonies or small, mucous, α-hemolythic colonies will be confirmed through Optochin-disk testing, bile susceptibility testing and latex agglutination test. Isolates will be further analyzed through molecular typing as described below. Isolates that will not be immediately tested will be freezed at -80°C in Wilkins-Chalgren broth + 20% glycerol for further analyses.

**Clinical follow-up**

Subjects will be considered colonized by S. pneumoniae with at least one positive nasopharingeal swab. Colonized patients will be followed for the next 12 months so to observe potential invasive infections. Potential simultaneous colonization by two or more serotypes will be highlighted through the analysis of isolated colonies.

**Analysis of isolates from nasopharingeal swab**

All the isolated strains of S. pneumoniae will be collected and subdued to antibiotic susceptibility testing following CLSI guidelines (Kirby-bauer disk diffusion tests, MIC susceptibility testing), and results will be interpreted following CLSI breakpoints. Susceptibility to recently introduced antibiotics (tigecycline, linezolid, quinupristin-dalfopristin) will be assessed. Strains will be also serotyped using sera obtained from SSI (Statens Serum Institut).

S. pneumoniae isolates will also be subdued to genotypic analysis. Genomic DNA from a fresh colture will be extracted with High Pure PCR Template Preparation Kit (Roche), then a multiplex PCR reaction will be performed so to deduce capsular serotype, as indicated by CDC (<http://www.cdc.gov/streplab/downloads/pcr-oligonucleotide-primers.pdf>). Clonalty of isolates will also be assessed through multi locus sequence typing (MLST), amplifying and sequencing seven housekeeping genes (aroE, gdh, gki, recP, spi, xpt and ddl) as indicated by MLST website ([http://www.mlst.net](http://www.mlst.net/)). PCR products will be purified, sequenced and results compared to international databases (<http://spneumoniae.mlst.net/>), allowing identification of different Sequence Types (STs) or performing phylogenic analysis of different STs through eBURST open-source software ([http://eburst.mlst.net](http://eburst.mlst.net/)).

We will also focus on other features of S. pneumoniae, such as the evaluation of molecular and phenotypic features amid isolates retrieved from invasive diseases. Moreover, a selection of Penicillin resistant S. pneumoniae (PNSSP) will be made and comparison against PSSP will be performed trough:

- PCR amplification of

-- PCR amplification of pbp2b, pbp2x genes (and pbp1a for PRSP strains)

-- restriction fragments length polymorphisms (RFLP) through Diversity DatabaseTM, Bio-Rad, version 2.2.0 software.

[figure not shown]

**STATISTIC ANALYSIS**

Clinical and anamnestic data collected at enrolment and at each follow-up visit, will be integrated with microbiological and serological results and correlation analyses will be performed.

Further statistical analyses will be carried out considering the results from this study and from the sub-study (protocol code PNEUMO-HIV 2011).

To evaluate the immunological response, the geometric mean concentrations of IgG (GMCs) at baseline, 4,8,24 e 48 week will be calculated. The GMCs will be compared by Student's' t Test (For Paired Samples). The quantitative variable will be tested for normal distribution and compared by

Mann-Whitney or Kruskal-Wallis test.

Differences in proportion will be determined by chi squared test or fischer exact test.

Regression or logistic analyses (univariate and multivariate) will asses the association with colonization, infection, antibiotic resistance, and an efficient immune response (e.g. ≥0.35μg/mL).

Analyses were performed using the SPSS software package (version 17.0 Chicago, IL).

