**STATISTIC ANALYSIS**

Clinical and anamnestic data collected at enrolment and at each follow-up visit, will be integrated with microbiological and serological results and correlation analyses will be performed. Further statistical analyses will be carried out considering the results from this study and from the main study (protocol code PCV13-HIV2011).

To evaluate the immunological response, the geometric mean concentrations of IgG (GMCs) at baseline, 4,8,24 e 48 week will be calculated. The GMCs will be compared by Student's' t Test (For Paired Samples). The quantitative variable will be tested for normal distribution and compared by

Mann-Whitney or Kruskal-Wallis test.

Differences in proportion will be determined by chi squared test or fischer exact test.

Regression or logistic analyses (univariate and multivariate) will asses the association with colonization, infection, antibiotic resistance, and an efficient immune response (e.g. ≥0.35μg/mL).

Analyses were performed using the SPSS software package (version 17.0 Chicago, IL).

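### The only antibody outcome named for the regression models is IgG cut at a threshold; an adjusted model of continuous log IgG should be specified as the main one

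*Supplement*

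**What the plan says.** Main study (PCV13-HIV2011), Immunological evaluations: the assay gives "Quantitation of specific IgG levels for 13 PCV13 serotypes", and "IgG concentrations will be expressed as geometric mean concentration (GMC"). The same section adopts a cut-off for seroprotection: "The generally used threshold of 0.35µg/mL (accepted by the WHO for assessment of vaccine efficacy against IPD) it will be chosen as cut-offs".

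Main study, Statistic Analysis: GMCs are compared between visits by paired t test. Quantitative variables, not named, are compared by Mann-Whitney or Kruskal-Wallis test. Correlation analyses of clinical and serological data are announced without detail. The modelling sentence reads "Regression or logistic analyses (univariate and multivariate) will asses the association with colonization, infection, antibiotic resistance", "and an efficient immune response (e.g. ≥0.35μg/mL"). The predictors are not listed. The sub-study (PNEUMO-HIV 2011), Statistic Analysis, repeats the sentence.

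Main study, Sample size and study group selection: "50 HIV-infected adult outpatients who had never been vaccinated with any pneumococcal vaccine will be prospectively enrolled". No alpha, power, SD, effect size or expected seroprotection rate is given.

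**The concern.** Colonization, infection and antibiotic resistance are yes/no by nature. Immune response is the one outcome in that sentence that is made binary by choice. Once it is cut at 0.35 µg/mL, 0.36 and 10 µg/mL count as the same result. The threshold is adopted to define seroprotection, which supports reporting a rate. Nothing in the documents explains why it should also be the outcome in a model of which patient factors go with a better or worse response.

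The loss grows as more vaccinees pass the threshold, because the logistic model learns only from the contrast between those above and those below. With 50 patients and 95% above, 50 × 0.05 = 2.5 patients are expected below. A factor that truly halves antibody levels could then be reported as not associated with response. Serological response is a primary outcome, so the question is not peripheral.

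**Working it through.** **Inputs from the documents.** N = 50 in the main study; IgG measured quantitatively; cut at 0.35 µg/mL. The 50 cannot be reproduced, because no inputs to it are stated.

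**Assumed inputs (none is in the documents).** A binary patient factor split 25/25; a true GMC ratio of 2, so a mean difference on the ln scale of ln 2 = 0.693; two-sided alpha 0.05; ln IgG normal with SD 0.8, 1.0 or 1.2 (0.35 to 0.52 on the log10 scale); 50% to 95% of patients above the cut.

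**Uncut analysis.** Two-sample t test on ln IgG, 48 df, critical value 2.01. The noncentrality is 0.693 / (SD × √(1/25 + 1/25)) = 0.693 / (0.283 × SD), which is 3.06, 2.45 and 2.04 for the three SDs. Power from the noncentral t is 85%, 67% and 52%.

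**With baseline ln IgG as covariate.** With an assumed correlation of 0.5 between baseline and post-vaccination ln IgG, and a factor unrelated to baseline, the residual SD is SD × √(1 − 0.5²) = 0.866 × SD. At SD 1.0 the noncentrality is 0.693 / (0.283 × 0.866) = 2.83, and power is about 79%.

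**Cut analysis.** Let m be the distance of the midpoint of the two group means above ln 0.35. The proportions above the cut are Φ((m − 0.347)/SD) and Φ((m + 0.347)/SD), with m set so that their average equals the chosen share. At SD 1.0 and an 80% share they are 0.71 and 0.89. Power is the sum of the binomial probabilities of all pairs of counts for which the likelihood-ratio statistic of the logistic model exceeds 3.84.

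| Share above the cut | SD 0.8 | SD 1.0 | SD 1.2 |
|---|---|---|---|
| Uncut ln IgG (any share) | 85% | 67% | 52% |
| 50% | 72% | 54% | 41% |
| 70% | 63% | 46% | 34% |
| 80% | 55% | 40% | 30% |
| 90% | 44% | 33% | 26% |
| 95% | 27% | 21% | 18% |

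The loss is smallest at a 50% share with SD 1.2 (52 − 41 = 11 points) and largest at a 95% share with SD 0.8 (85 − 27 = 58 points).

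**Dependence on the test.** At SD 1.0 and shares of 50/70/80/90/95%, the Wald test of the logistic coefficient has about 47/42/28/4/<1% power, and the Fisher exact test 42/33/26/9/1%. The Wald figures collapse because one cell of the 2 × 2 table is empty in about 33% of trials at a 90% share and 67% at 95%. The likelihood-ratio figures are themselves approximate in such sparse tables.

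**Larger SDs.** At a log10 SD of 0.6 and 0.7 (about 1.4 and 1.6 on the ln scale), even the unadjusted uncut analysis has only 41% and 32% power. It would need 63 and 85 patients per group for 80%.

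Not modelled: several covariates, dropout and 13 serotypes. These would generally lower power for both approaches.

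**The case against.** The plan is loosely worded rather than committed to a cut. It offers regression as well as logistic models, and 0.35 µg/mL is introduced as an example. This stands: a reader might infer that the plan rules out a continuous response model, and it does not. But none is specified, any other threshold would still be a cut, and an open threshold could be chosen after the data are seen.

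IgG is also analysed uncut elsewhere. The paired t test compares visits within patients and says nothing about patient factors. The correlation analyses and rank tests could relate factors to IgG. In the two-group setting above at SD 1.0, Mann-Whitney on uncut IgG has about 65% power, close to the t test. So the regression models cannot be called the only planned look at patient factors. What is missing is an adjusted continuous model, which rank tests do not supply.

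A reader might also infer that a twofold difference would usually be missed, or that power is practically nil when 90% or more pass the cut. The documents support neither. At SD 0.8 with 80% or fewer above the cut, likelihood-ratio power is 55% or more. The near-zero values belong to the Wald test in sparse tables, and the plan does not name that test.

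Finally, who reaches a WHO-accepted threshold is a legitimate question, and this is a pilot study. Both are true, and the fix keeps that analysis.

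**Conclusion.** The point holds as a matter of specification and efficiency. IgG is measured in full, the only antibody outcome named for the regression models is a dichotomy, and no adjusted continuous model is specified in either study. Under the assumed inputs the cut costs about 11 to 58 percentage points of power by likelihood ratio, and most where most vaccinees pass the threshold. The direction is the same in every scenario examined; the size depends on an SD, an effect and a seroprotection rate that the documents do not give. The cut is not the only limit: at larger SDs 50 patients are too few for a twofold difference even when IgG is left uncut. The change should be made, but the flaw does not invalidate the trial.

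**What to change.** In the Statistic Analysis sections of both the main study and the sub-study, state that the main association model for immune response is a linear regression of log-transformed serotype-specific post-vaccination IgG on the patient factors, with log T0 IgG as covariate. Name the visit in advance, and report effects as GMC ratios with 95% confidence intervals. In the sub-study the model applies to the vaccinated HIV-positive patients only, since HIV-negative subjects are sampled only at baseline. Keep the proportion at or above 0.35 µg/mL as a seroprotection rate, with the logistic model on it as supportive.

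The cost is about two sentences in each section. T0 and follow-up sera are already collected, no further patients or samples are needed, and SPSS fits the model. The small downside is that effects are read as GMC ratios rather than odds of seroprotection, and residuals on the log scale must be checked.
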